## Abstract

**Background:** Hallmarks of alcohol use disorder (AUD) are disturbances of circadian rhythms and everyday structures. While circadian rhythms dictate the timing of daily recurring activities such as sleep, activity, and meals, conversely, these activities represent time cues, so called *Zeitgebers*, that the circadian system uses to synchronize with the environment. Here we present a study protocol for our newly developed therapy approach for AUD patients, in which we take advantage of this mutual influence and stabilize and strengthen their circadian system by creating strict daily schedules for daily *Zeitgeber* activities. Since every person has a circadian system with its own characteristics and is subject to social obligations, the daily plans are personalized for each test person. Our hypothesis is that a regular exposure to *Zeitgebers* stabilizes behavioral and physiological circadian rhythms and thereby reduces the risk of alcohol relapses and depressive symptoms and facilitates physical recovery in AUD patients during the 1st weeks of their addiction therapy.

**Methods/design:** The study is a 6-weeks single site trial with a controlled, randomized, single-blinded, parallel-group design including patients with a diagnosis of AUD. The study runs parallel to the standard addiction therapy of the clinic. Patients are randomly assigned to either an intervention group (DAILY) or a sham control group (placebo treatment). Questionnaires and physiological assessments of both groups are conducted before and immediately after the intervention or control treatment. According to our hypothesis, the primary outcomes of this study are improvements of regularity, alcohol consumption, and relapse rate in AUD patients compared to AUD patients receiving control treatment. Secondary outcomes are reduced depressive symptoms and increased physical recovery.

**Discussion:** This study is a randomized controlled trial to investigate the efficacy of a personalized circadian *Zeitgeber* therapy as an adjunctive treatment for alcohol use disorder patients. The overall goal of this and more extended future studies is the development of an adjunctive therapy for AUD patients that is uncomplicated in its use and easy to implement in the clinical and everyday routine.

**Trial registration:** This study is registered at the German Clinical Trial Register with the trial number DRKS00019093 on November 28, 2019.

## Background

### Harmful Use of Alcohol and Alcohol Use Disorder

Harmful use of alcohol and alcohol use disorder (AUD) lead to increased morbidity and mortality. According to the World Health Organization (WHO), 5.1% of all disorders, diseases, injuries, and 5.3% of all deaths are attributable to alcohol consumption (1). Typical disorders and diseases associated with harmful alcohol consumption and AUD include cardiovascular, infectious, neurological diseases, cancer, and psychological disorders such as depression and anxiety (2, 3). Impressively, as a result, mortality due to alcohol consumption is higher than for other serious diseases such as HIV or tuberculosis (1). In addition to the adverse health effects of those concerned, this also means that, at the societal level, harmful alcohol consumption behavior creates a significant burden on the economy and health systems (4, 5).

### The Circadian System

Endogenous circadian clocks (from Latin *circa diem*, about a day) have evolved to prepare organisms to daily recurring environmental changes caused by the rotation of the earth around its axis. Circadian clocks are found in almost all cells of the body and since they regulate the expression of about 50% of our genes (6), there is almost no process in the body that is not under their influence. In humans, the master circadian clock is located in the suprachiasmatic nucleus (SCN) in the anterior part of the hypothalamus (7–9). The SCN acts like a conductor of an orchestra and sets all other cellular clocks in the rest of the body to an appropriate period and phase (10). Synchronization of endogenous circadian rhythms with environmental 24-h cycles is achieved through so called *Zeitgebers* (German: time givers) (11). The strongest stimuli that serve as *Zeitgebers* are light and food, whereby light acts directly on the SCN. In a simplified model, the SCN, in turn, determines sleep and wake times and when hunger arises. The ingested food then entrains peripheral clocks. Physical activity (exercise) and social contact are also regarded as *Zeitgebers*, but weaker ones (12). In an optimal situation, molecular, physiological, and behavioral rhythms are synchronized among each other and with the environment (13). Since the circadian clock is involved in virtually all bodily processes, their perturbation is strongly associated with a high number of disorders, including mental illnesses such as AUD or major depressive disorder (MDD) (13, 14).

### Association of Circadian Clocks and Alcoholism

In recent years evidence emerged that there is a bidirectional relationship between circadian rhythms and alcohol consumption (15). AUD patients often suffer from circadian misalignment, which, in turn, is known to increase the risk of developing AUD (15–17).

On the one hand, individuals with AUD almost always suffer from disorders of the circadian system, such as disturbed sleep times, impaired sleep quality, altered molecular rhythms, and altered daily rhythms of neuroendocrinological functions in different regions of the brain (18). Even acute alcohol drinking can cause spontaneous alterations in circadian rhythms (19), and circadian rhythms are also affected during alcohol withdrawal (20, 21). Importantly, alcohol-dependent patients have a higher risk of relapse during withdrawal if their internal clock is disturbed (18). On the other hand, disrupted circadian rhythms are considered a strong risk factor for the development of AUD, as disturbances of circadian sleep-wake cycles are frequently observed in subjects with a late chronotype and shift workers show an increased prevalence of harmful use of alcohol and AUD (19). Moreover, single nucleotide polymorphisms in the clock genes Clock, Per2, and Per3 genes have been associated with alcohol consumption behavior (22, 23).

Curiously, although AUD patients generally suffer disturbances of molecular and behavioral rhythms, their need for alcohol often follows circadian patterns with around 80% of alcohol addicts having their first drink at a specific hour with low variability (17, 24–27). Accordingly, in rodents, the regular administration of drugs can trigger anticipatory locomotor activity before the drug is actually provided, which suggests the existence of a drug-entrainable oscillator (24).

In summary, AUD patients have disturbed circadian rhythms in daily sleep and neuroendocrinological rhythms on the one hand, but on the other hand are strongly entrained by alcohol. Together, these data highly suggest an imbalance of *Zeitgeber* signals in AUD patients. While light, food, and physical activity are usually the strongest *Zeitgebers*, in AUD patients these may lose influence and be replaced by alcohol. Thus, a targeted amplification of the other *Zeitgebers* can possibly reduce the influence of the *Zeitgeber* alcohol and thereby reduce symptoms of AUD patients during withdrawal and help to reduce relapses.

### Biological Mechanisms Targeted With a Circadian *Zeitgeber* Therapy in AUD Patients

In recent years, there has been growing evidence that circadian rhythms modulate reward circuits and behavior (28–31). For instance, the activation of reward processing is subject to circadian control (32), the release of neurotransmitters, such as dopamine and serotonin, varies over the course of the day, and dopamine signaling in the SCN has strong impact on its rhythms and processing responses to hedonic stimuli (33, 34). Thus, in animals and humans, depending on the time of day, rewards are valued differently (35) with the consequence that sensitization and motivation toward rewarding stimuli change over the course of 24 h (32, 36–38). Moreover, in humans, under constant conditions, it was shown that rhythms of the diurnal positive affect parallels rhythms of core body temperature, further suggesting endogenous circadian control of reward motivation (39).

Because of the close connection to the reward system, it is not surprising that circadian clocks have also been associated with addiction and alcohol use (16, 40, 41). Circadian misalignment in humans can be proven and quantified by the discrepancy between the phase angles of the dim light melatonin onset (DLMO) and the sleep offset. Interestingly, the more pronounced the circadian misalignment is, the greater the severity of substance abuse and dependence (42). It is also remarkable that melatonin levels, which are usually high at night, are inverted in AUD patients under the influence of alcohol and during acute withdrawal, which further indicates severe circadian disturbances in AUD patients (43). Moreover, circadian misalignment due to a late chronotype is also associated with increased impulsivity, which is a risk factor for the development of AUD (44, 45). Furthermore, it was shown that at certain times of the day, craving is particularly pronounced, since our reward system follows a circadian pattern (27).

In rodents, drug reward displays daily rhythms (46). These rhythms are associated with oscillating expression of the dopamine transporter and are directly related to clock gene expression in the medial prefrontal cortex and mesolimbic dopaminergic system (47). Mice exposed to chronic circadian disruption display reduced neuronal complexity in prelimbic prefrontal brain areas and reduced behavioral inhibition, which again is associated with increased alcohol consumption (48).

The above described studies indicate the existence of a neurobiological circadian-reward system, which in case of disruption can contribute to the development and maintenance of addiction disorders (40). Therefore, our therapeutic approach aims to synchronize circadian rhythms of the entire body among themselves and with the environment by a very regular exposure to *Zeitgebers* (light, dark, food, and if applicable activity). In a stable light-dark cycle, the SCN entrains robustly to it, and can reliably transmit these time signals to the rest of the body. Additionally, food is a very potent *Zeitgeber*, and regular mealtimes can entrain clocks of most peripheral organs as well as many brain oscillators (49, 50). Among those are brain areas that are involved in motivational responses to food and the SCN (51, 52). Consequently, strictly timed food has already been suggested as chronotherapeutic approach to improve circadian disruptions in populations such as shift workers (53, 54).

### Circadian *Zeitgeber* Therapy for AUD Patients in the Transition From Inpatient to Outpatient Care

For AUD patients, the transition phase between the inpatient stay and discharge from the clinic to outpatient care or home often represents a stressful and thus susceptible time for alcohol relapses and a worsening of the general psychiatric health situation (55). For patients the sudden change from the clinical environment back to autonomous self-organized daily routines is often very difficult (56). During this transition phase, daily rhythms such as sleep-wake cycles and mealtimes become irregular and often drift into a later phase, which has been associated with a worsening of psychiatric symptoms, including alcohol relapses and depression (57, 58).

Within the framework of psychotherapy the suggestion of structuring the everyday life in an orderly manner to psychiatric patients, especially AUD patients is not new (59). This therapy component of self-management has positive psychological effects such as reducing stressful situations and enhancing the feeling of self-efficacy. However, we have designed a study that, in addition to previous therapy programs, has a special focus on the transition time between inpatient and outpatient care or home, and which focuses on the targeted use of strong *Zeitgebers* to restore and stabilize physiological circadian rhythms in AUD patients. Similar circadian reinforcement therapies have been proven for bipolar disorder (60, 61) and are currently tested in a study for MDD (62). However, the development and systematic investigation of a circadian structure therapy for AUD patients has not yet been published and was recently highlighted as a necessity (63). Thus, with DAILY we develop a new treatment approach for AUD patients, partly based on established concepts of chronotherapies for other mental disorders and implement it alongside standard AUD therapies.

We assume that subjects in our study benefit from the reduction of physical conditions that promote and maintain alcohol consumption behavior. We further believe that the strengthening of circadian rhythms has not only positive effects on alcohol craving, but also on often accompanying symptoms of AUD, such as depressive mood. Therefore, we have called this newly proposed intervention for AUD patients DAILY, which stands for **D**epression **A**lcohol **Il**lness Therap**y**.

## Study Hypotheses and Objectives

Our primary hypothesis is that a regular exposure to *Zeitgebers* stabilizes circadian behavioral rhythms and thereby reduces alcohol consumption and the risk of alcohol relapses in AUD patients. Accordingly, the primary objectives of the study are to determine whether the intervention program DAILY decreases day-to-day variations in behavior and reduces alcohol consumption and the relapse rate in AUD patients compared to those receiving control treatment. Furthermore, we hypothesize that the regular exposure to *Zeitgebers* contributes to the reduction of depressive symptoms and a subjective and physiological well-being in AUD patients, which in turn positively affects the primary objectives of the study. Accordingly, the secondary objective of the study is to ascertain whether the DAILY program supports the surrogate criterions of increased sleep quality, reduced depressive symptoms, increased self-efficacy expectations, and improved blood-values that are associated with harmful alcohol consumption. We also hypothesize, that additional psychoeducation about biological mechanisms in the development of AUD helps participants to complete their current therapy and maintain compliance. Therefore, as exploratory outcomes, we will investigate whether more participants of the intervention group accomplish the DAILY therapy than participants of the control group. Finally, we will assess whether the DAILY intervention has impact on the chronotype of the participants, although it is not a specific aim of our treatment to change it.

## Study Design

### Design

The study is a 6-weeks trial with a controlled, randomized, single-blinded, parallel-group design including patients with a diagnosis of AUD. Patients are randomly assigned to either an intervention group (DAILY) or a sham control group (placebo treatment). As this study represents a pilot randomized trial, which does not primarily focus on proving treatment successes but more on ascertaining the best options for the future main trial, we will include each eligible patient within this year instead of using formal power calculations (64).

### Setting

DAILY is a single site study conducted at the specialist ward for addiction disorders and the outpatient clinic for substance use disorder of the Clinic for Psychiatry and Psychotherapy at the University Hospital of Munich. There are 24 patients with a minimum age of 18 years on the ward, with men and women admitted equally. The day clinic treats 15 patients with a minimum age of 18 years simultaneously. On the ward and in the day clinic there are fixed, individually determined schedules for therapy sessions from which patients are not allowed to deviate. Meals are offered by the clinic at fixed times of the day, but do not have to be taken. Patients are free to leave the ward and the day clinic between therapy sessions in order to take meals outside or to pursue other activities such as walks or sports. The ward is open in principle, but care is taken to ensure that patients do not leave it between 10 pm and 8 am. There are no fixed sleeping hours on the ward, except that patients must arrive on time for their therapy sessions, which usually start between 08:30 and 11:00 am. On the weekend, patients of the ward have no regular appointments. Patients of the Day Clinic leave the clinic in the afternoon and arrange the rest of the day and their weekends independently. In addition, food can be brought to the ward and the day clinic and snacks can be eaten at any time. Both clinics are interdisciplinary staffed by medical doctors, psychologists, nurses, and social workers, all of whom have broad experience in the treatment of substance use disorders, including AUD. About half of the patients on both sites are diagnosed with AUD, the other half suffers from multidrug dependency. On the ward a qualitative detoxification program with psychotherapeutic services is offered to AUD patients and patients with multidrug use. In the day clinic the same psychotherapeutic services are offered as on the ward, but the patients are already detoxified, and the therapy takes place on a day-care basis.

### Standard Therapeutic Services on the Ward and the Day Clinic

In parallel to the DAILY or the sham treatment, all patients receive the standard clinical treatment consisting of medical and psychological consultation, individual and group therapy (combining Motivational Enhancement Therapy and Cognitive Behavioral Therapy), and medication if necessary. The psychotherapeutic treatment of AUD and multiple substance use patients is the same but is conducted separately. The standard psychotherapy concept of the ward and the day clinic includes motivation work in which the incentive to abstinence and the decision to change consumption behavior is increased. In addition, situation analyses, the identification of risk factors, and the development of alternative actions are used to work with patients on relapse prevention. In addition, all patients receive psychoeducational therapy sessions to provide theoretical knowledge about the definition of addiction and its development on a neurobiological level. The treatment of AUD patients on the ward is scheduled for 14 days. In the day clinic, the treatment time ranges from 2 to 4 weeks and the concepts described above are elaborated in more detail and sociotherapy is also offered. In none of these standard therapies the advantages of daytime structures and regular sleep times are discussed.

### Study Population

Men and women, unemployed and employed subjects are equally included in the study. Depending on whether the subjects are patients of the ward or day clinic, they are in detoxification or post-detoxification treatment. Study enrollment of subjects who are newly admitted to the detoxification program of the ward will take place at the earliest after 5 days of detoxification, to exclude cognitive and physical limitations caused by acute intoxication and its after-effects. Study participants who are discharged from the ward either go home, receive further treatment in the day clinic, or go to other institutions for long-term therapy. Study participants who are discharged from the day clinic either go home after discharge or go to other institutions for further treatment. The health conditions of all test persons allow them to perform their daily tasks without external assistance. Approximately half of the study subjects have a regular job, while the others are unemployed or retired. Usually 3–5 subjects are involved in the study simultaneously.

### Eligibility Criteria

All persons are considered eligible on whom the below exclusion criteria do not apply. Subjects are only included in the study if they can assess the nature and scope of the investigations. Written consent is required for inclusion. The study is conducted in accordance with the principles of the Declaration of Helsinki with its amendments of Tokyo, 1975, Hong Kong, 1989, Somerset West, 1996, Seoul, 2008, and Fortaleza, 2013. The subjects must fulfill diagnostic criteria for AUD according to ICD-10 F10.2 and be of age 18–75 years. Smokers are eligible for this study. In case of dependency on other substances, the subjects must have been abstinent from these substances for at least 12 months at the time of study enrollment. One outcome of this study is the change in depressive symptoms in the subjects. For this reason, AUD patients with concomitant diagnosed MDD as well as substance-induced depression are included. However, a diagnosed depression is not a prerequisite for inclusion in the study.

### Exclusion Criteria

Excluded are subjects who are unable to give their consent, are pregnant, or are currently working in shifts. In addition, intellectual, neurological, or physical impairment that lead to the inability to independently perform tasks of daily life lead to exclusion of the study. In general, dependence on help with eating or going to bed (e.g., bedridden patients) precludes participation in the study. However, patients with disorders like liver damage, tremors, digestive problems, and blood abnormalities, which are common in AUD patients but do not lead to constant dependence on support from others, are not excluded. Blind subjects and patients with diagnosed mental illnesses other than AUD and MDD are generally excluded from the study. Patients with a dependence on other substances (except alcohol and nicotine) which they have consumed within the last 12 months are also not ineligible. The use of benzodiazepines, agomelatine, or medically prescribed cannabinoids will result in exclusion from the study, the use of other medications will not affect eligibility. Although patients with depressive symptoms are generally eligible for the study, no psychotic symptoms or acute suicidal ideation should be present. Subjects must not participate in other studies that may interfere therapeutically with the DAILY study.

## Study Procedure

The study procedure for the study participants is shown in Figure 1. The basic procedure is the same for participants of the intervention and control group.

**Figure 1 F1:**
[figure not shown]
Procedure of the DAILY study. Patients are screened and recruited by a member of the study staff. After 1 day at the earliest the participants sign the consent form. On this day, they are informed about the contents of the study; the contents discussed differ between intervention and control group. In addition, questionnaires are filled out and blood is drawn. During the week, a psychoeducation session takes place in which the contents and the aims of the study are deepened, further questionnaires (Table 1) are filled in, and a test diary is handed out to record times of daily actions which act as *Zeitgebers*. After at least 1 week, the diary is evaluated and a daily structure plan for regular exposure to *Zeitgebers* is worked out together with the test persons, to which they should adhere for the next 4 weeks. Subjects in the control group are not given instructions on how to structure their daily routine but are still asked to complete the diary. At least one telephone appointment is made for the time the subjects fill out the diaries to maintain compliance. After 4 weeks, there will be a final personal appointment where the diaries will be collected, all questionnaires will be repeated, and blood will be drawn again.

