### Informed Consent and Baseline Assessments

To participate in the study, all participants need to sign an informed consent in the 1st week (Figure 1). Afterwards, irrespective of the group allocation, a semi-structured interview is conducted to assess demographical data: age, gender, employment status, occupation, and marital status. Medical data are evaluated as well: size, bodyweight, blood pressure, current medications, and information about previous alcohol problems and possible depressive episodes. In addition, the questionnaires described below (Table 1) are filled out together with the participants. Lastly, blood samples are collected. This appointment is also used to prepare the test persons for the topics and contents of their respective groups.

**Table 1 T1:** Overview of questionnaires, physiological assessments, and time points.

**Assessment category**	**Assessment instruments**	**First session**	**Last session**	**Between sessions**
Baseline	Demographics	x		
Circadian	Sleep-Food-Diary			x
	Munich ChronoType Questionnaire (MCTQ)	x	x	
	Pittsburgh Sleep Quality Index (PSQI)	x	x	
Alcohol use	Alcohol use disorders identification test (AUDIT)	x	x	
	European Addiction Severity Index (EuropASI)	x	x	
	Timeline Followback 30 (TLFB)	x	x	
Depression	Hamilton Depression Scale (HAMD)	x	x	
	Inventory of Depressive Symptomatology (IDS-SR)	x	x	
Self-efficacy	Self-Efficacy Questionnaire (SWE)	x	x	
Blood values	Blood draws	x	x	

The further course of the study and the contents of the following appointments are described separately for the intervention group and the control group.

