### Intervention Group

#### Week 1: Psychoeducation and Test Diary

After baseline assessments, a few days later in the same week, the test persons participate in individual 1-h psychoeducation sessions about circadian clocks and their effects on health and psychiatric disorders, such as addiction and depression. The scientific content is communicated in simple language. Firstly, the participants get explained that circadian rhythms can be found virtually everywhere in nature and that they have impact on essentially all physiological processes, including sleep-wake cycles, hunger, digestion, wound healing, cellular functions, and molecular processes. A focus is on their involvement in neurobiological systems, such as reward, addiction networks, and behaviors. During the session, the test subjects are led to understand how important regular daily routines are for mental and physical health. Therefore, the study assistant emphasizes the importance of certain environmental cues that can serve as *Zeitgebers*, such as light and food. Together with the participants, the impact of light on sleep is discussed and how light can be avoided at late hours (e.g., by stopping the use of mobile phones, watching TV, or playing computer games after sunset or by using blue-light filters). Furthermore, the importance of regular mealtimes is discussed as food is an important *Zeitgeber* for many organs, including brain areas involved in the development of addiction. At the end of this session, the study assistant hands out a circadian diary (Supplementary Table 1), which the participant is asked to fill out for 1 week. With the help of the diary, data on times of meals, snacks, activity times, sleep duration, sleep quality, mood, and alcohol craving are collected on a daily basis. At this point in time, the test persons do not yet receive any concrete instructions as to when they should execute activities. Rather, they are instructed to use the following days to see if they can recognize certain temporal patterns in their own behavior and to consciously follow these patterns. Filling out the test diary serves on the one hand to create an awareness of their own daily rhythms. Besides, it gives the test persons the opportunity to familiarize themselves with the filling out of the diary. On the other hand, the data obtained on eating and sleeping times can be used in the next session as a basis for drafting a daily structure plan.

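### The Figure 1 legend places some Table 1 baseline questionnaires at the psychoeducation session, against Table 1 and the text, and nowhere are baseline forms required to precede arm-specific content

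*Protocol article*

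**What the plan says.** The Figure 1 legend (Study Procedure) spreads the questionnaires over two contacts. On the consent day, "In addition, questionnaires are filled out and blood is drawn". Later that week, "a psychoeducation session takes place in which the contents and the aims of the study are deepened, further questionnaires (Table 1) are filled in".

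The section Informed Consent and Baseline Assessments has one appointment, with the interview and blood sampling: "In addition, the questionnaires described below (Table 1) are filled out together with the participants". Table 1, titled "Overview of questionnaires, physiological assessments, and time points", marks every questionnaire for the first and the last session. Only the diary is marked between sessions. The intervention-group section for week 1 then says: "After baseline assessments, a few days later in the same week, the test persons participate in individual 1-h psychoeducation sessions". The only paper it mentions in that session is the diary.

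Both accounts also place group-specific content on the consent day. The legend says of the information given then that "the contents discussed differ between intervention and control group". The baseline section says: "This appointment is also used to prepare the test persons for the topics and contents of their respective groups".

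**The concern.** A start value should be measured before the treatment can act on it. Psychoeducation is the first of the three main components of DAILY listed in the Discussion. In the DAILY arm, "the test subjects are led to understand how important regular daily routines are for mental and physical health", and the session also covers light and sleep, addiction and depression. The control arm talks about legal drugs in society and alcohol advertising instead (Control Group). A form filled in at this session may already carry an effect of the teaching, or of the expectations it raises, and that effect can differ between arms.

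Sleep quality, depressive symptoms and self-efficacy are secondary objectives and are measured by Table 1 questionnaires. The second analysis under Data Analysis compares the arms on change from start to end, so a displaced start value enters it directly. The article also describes the study as a pilot for a main trial, so an unresolved baseline schedule could be carried forward.

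**Working it through.** The article gives no figure for this point, so the check is a comparison of its statements.

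**1. Where the questionnaires are placed**

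| Source | Placement |
|---|---|
| Figure 1 legend | Some on the consent day, further Table 1 forms at the psychoeducation session |
| Table 1 | MCTQ, PSQI, AUDIT, EuropASI, TLFB, HAMD, IDS-SR, SWE: 8 of 8 at first and last session, none at a psychoeducation session |
| Informed Consent and Baseline Assessments | Table 1 forms at the baseline appointment |
| Week 1 | Psychoeducation a few days after baseline, diary handed out, no questionnaire mentioned |
| Weeks 3–6 | The final visit repeats the first session's questionnaires |

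The legend puts at least one of the eight at psychoeducation and the other sources put none there. Both cannot be followed.

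**2. Is there an innocent explanation?** The 30-item structuredness questionnaire (Measured Outcomes) could have been the further form, but it is not in Table 1 and the legend cites Table 1.

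**3. Does the text version give a clean baseline?** Not by its wording. The forms and the preparation for the assigned group share one appointment, and no order is stated.

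**4. Which analyses are exposed?** Let B be the mean start value and E the mean end value, with subscripts D (DAILY) and C (control). Let δ be the mean shift in the start value caused by content already received.

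- Endpoint comparison: E_D − E_C. It contains no B and is unaffected.
- Change comparison: (E_D − B_D) − (E_C − B_C). With shifted start values it becomes [E_D − (B_D + δ_D)] − [E_C − (B_C + δ_C)], which is the intended contrast minus (δ_D − δ_C).

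The bias is therefore −(δ_D − δ_C). It vanishes if the two sessions shift answers equally. If DAILY teaching already improves reported mood or sleep, the benefit on change is understated. If it makes patients notice and report more problems, the benefit is overstated. The article gives no value for either δ, so size and sign remain open.

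**5. Which instruments are most exposed?** The legend does not name the deferred forms. Judged by the descriptions under Measured Outcomes, TLFB counts drinks and alcohol-free days over the past 30 days, AUDIT covers recent drinking habits and HAMD is rated by an assessor, so one session is less likely to move these. PSQI, IDS-SR and self-efficacy are the more plausible candidates. The Routine Variability Score comes from the diary and does not depend on these forms.

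**The case against.** The strongest reply is that one clause in a legend stands against several consistent statements, and that the detailed account of the session lists only the diary. Loose legend wording is a reasonable explanation, and the figure itself cannot be seen here. This stands as a reason not to claim that any baseline was contaminated. It does not remove the contradiction, because the Study Procedure section refers the reader to Figure 1 for the procedure.

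A second reply is that the legend does not say the forms follow the teaching within the session. That is correct. Forms filled in at its start would precede the hour of psychoeducation. They would still follow the group-specific information of the consent day, which the legend says is then deepened.

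A third reply is that the control group has a parallel session, so timing is balanced between arms. That is also correct. The issue is different content at the same time, not different timing.

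A reader might infer that part of the DAILY baseline is in fact measured after treatment, or that a definite share of the effect is lost. The article supports neither. The first depends on which text staff follow and on the order within a visit. The second needs effect sizes that the article does not give. A reader might also infer damage to a baseline-adjusted comparison of the arms, but Data Analysis names no such model.

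**Conclusion.** The inconsistency is certain. The bias is conditional. It arises if the legend is followed, or if group-specific preparation at the first appointment comes before the forms, and if that content shifts answers differently in the two arms. Under those conditions the start-to-end change comparison is biased by an amount and in a direction that cannot be computed from the article, mainly for PSQI, IDS-SR and self-efficacy. The endpoint comparison stands either way.

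The point is worth correcting because the remedy costs little and the order of the first appointment needs to be fixed whichever version was intended.

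**What to change.** - In the Figure 1 legend, delete the clause on questionnaires from the psychoeducation step.
- In the legend, in Informed Consent and Baseline Assessments and in Table 1, state that all baseline questionnaires are completed before any arm-specific content, including the preparation on the consent day. Deleting the clause alone would not secure this.
- If one visit is too long, split the forms over two appointments that both precede arm-specific content.
- For patients already enrolled, use the completion date of each baseline form to flag those completed on or after the day of the psychoeducation session, and run a sensitivity analysis of the change comparison on that basis. Dates will not show the order within the first appointment, so that part can be secured only for future patients.

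The cost is wording, a fixed order of existing forms, and a somewhat longer first appointment or one more short one.
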